### Assessments and Outcomes

Prospective participants will complete a brief eligibility screening questionnaire in REDCap, which includes basic demographic items (eg, age and sex) and questions aligned with study inclusion/exclusion criteria (eg, “Do you speak English fluently?”). Study assessments will be administered electronically via REDCap at 4 time points: baseline, brief check-in surveys at the end of weeks 2 and 4, and 6-week follow-up. Intervention participants will also be invited to complete an optional postintervention feedback interview via Zoom or telephone.

A description of study measures, including assessment time points, is shown in Table 1. See Figure 2 for the enrollment and intervention schedule.

**Table 1. T1:** Description of survey instruments based on the stress process model [13].

Domain and measure		Time points			
		S^a^	BL^b^	Weeks 2 and 4	FU^c^
Background and context					
Sociodemographic characteristics					
Single-item assessments (age, sex, race/ethnicity, education, geographic location, income, and kinship to care recipient)		✓	—^d^	—	—
Technology proficiency					
Mobile Device Proficiency Questionnaire-16 [51]		—	✓	—	—
Primary stressors: objective					
Functional dependency					
Katz Activities of Daily Living Scale [52,53]		—	✓	—	✓
Lawton-Brody Instrumental Activities of Daily Living Scale [54]		—	✓	—	✓
Caregiver Medical and Nursing Task Inventory [55,56]		—	✓	—	✓
Cognitive impairment					
Revised Memory and Behavior Problems Checklist [57]		—	✓	—	✓
Primary stressors: subjective					
Relational deprivation					
Relational Deprivation Scale [13]		—	✓	—	✓
Secondary stressors: role and intrapsychic strains					
Family conflict					
Family Conflict Scale [13,58]		—	✓	—	✓
Employment conflict					
Job-Caregiving Conflict Scale [13]		—	✓	—	✓
Mood					
Positive and Negative Affect Schedule [59]		—	—	✓	—
Preparedness					
Preparedness for Caregiving Scale [60]		—	✓	—	✓
Cost of care					
Cost of Care Index–Economic Costs Subscale [61]		—	✓	—	✓
Surrogate decision-making					
Advance Care Planning Engagement Survey-9 [62,63]		—	✓	—	✓
Self-care					
Self-Care of Informal Caregivers Inventory [64]		—	✓	—	✓
Role confusion					
Role Captivity Scale		—	✓	—	✓
Predeath grief					
Prolonged Grief Disorder-12 Caregiver Version [65,66]		—	✓	—	✓
Caregiver burden					
Zarit Burden Interview-12 [67]		—	✓	—	✓
Caregiving rewards					
Positive aspects of caregiving [68]		—	✓	—	✓
Mediators					
Caregiver needs					
CarePair needs assessment^e^		—	✓	—	✓
Social support					
Lubben Social Network Scale-6 [69]		—	✓	—	✓
Formal support					
Negative service attitudes and experiences [70]		—	✓	—	✓
Satisfaction with the types and quality of services [71]		—	✓	—	✓
Prior use of services, willingness to use services, and types of services used^e^		—	✓	—	✓
Primary outcomes					
Feasibility					
Recruitment: number/proportion screened, eligible, consented/enrolled, declined, and retained [72]		—	✓	—	✓
Usability: System Usability Scale (SUS) [73,74]; user version of the Mobile Application Rating Scale (uMARS) [75]		—	—	—	✓
Intervention adherence: app usage (measured via number of log-ins); feature usage (measured via number of interactions with resources [eg, saves and notes])		—	—	—	✓
Acceptability					
Satisfaction and acceptability survey^e^		—	—	—	✓
Secondary outcomes					
Depression					
Patient Health Questionnaire-9 [76]		—	✓	—	✓
Patient Health Questionnaire-2 [76,77]		—	—	✓	—
Anxiety					
Generalized Anxiety Disorder-7 [78]		—	✓	—	✓
Generalized Anxiety Disorder-2 [78]		—	—	✓	—
Caregiver stress					
Kingston Caregiver Stress Scale [79,80]		—	✓	—	✓
Self-efficacy					
Revised Scale for Caregiving Self-Efficacy [81]		—	✓	—	✓
Quality of life					
Satisfaction with Life Scale-5 [82]		—	✓	—	✓
Satisfaction with Life Scale-1 [82,83]		—	—	✓	—

a S: screening survey.

b BL: baseline survey.

c FU: 6-week follow-up survey.

d Not applicable.

e Developed for this study.

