### Study Conditions

Participants will be randomly assigned to the intervention group or the attention control (Digify) group. Both groups will log into their assigned platform (CarePair or Digify) twice per week and read 1 article per log-in (12 articles total across the intervention) for the 6-week study period. Participants will access their respective platform via their personal smartphone device.

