### Intervention Group

Participants assigned to the intervention group will have access to the CarePair app. Over the 6-week study period, they will be instructed to log in twice per week to read and engage with 1 article per log-in session (eg, by rating, commenting, saving, or taking notes). Participants will also be encouraged, but not required, to explore and engage with service referrals available through the platform. Backend data will be collected to measure app engagement, including participants’ number of log-ins, time spent engaging with materials, specific content accessed, and feature interactions.

The onboarding process will direct caregivers to create a profile for themselves and their care recipients, choose an avatar, and select service preferences (eg, modality, cost, distance based on zip code, and time of the day). Users will also be prompted to complete a 12-item assessment (administered at pre- and postintervention)—the content of which was informed by studies 1 and 2 described above—to measure the primary domains caregivers reported needing assistance with. Each item begins with the stem “In your role as a caregiver, how much support do you need with…” followed by items such as “Understanding your care recipient’s brain change?” and “Dealing with your own feelings and worries?” Response options range from 1 (no need) to 4 (high need).

Following the initial onboarding session, users will be provided with an in-app tutorial that introduces the platform’s primary features (see Figure 1 for screenshots of the CarePair app interface). The *Home* page provides a personalized feed of resources curated algorithmically based on the user’s reported needs and preferences. The *Services* tab includes a catalog of local and virtual services tailored to caregivers’ profile preferences and assessment responses gathered during onboarding. The *Library* tab allows participants to browse through the app’s vetted ADRD- and caregiving-related resources, thematically organized by domain and relevance. Both the *Services* and *Library* pages allow users to add filters by category (eg, social support, legal, education, and grief).

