### Control Group

Participants in the attention control group will access a digital folder of articles via Digify, a secure document-sharing platform that allows for controlled access of materials and user-engagement tracking on metrics, including log-ins, articles read, and time spent viewing articles. This folder contains most articles available in CarePair, all focused on ADRD and caregiving topics (3 articles with video components were excluded as these formats are not supported by Digify), but they are not organized by relevance or tailored to caregivers’ needs. Control participants follow the same engagement schedule as participants in the intervention group (ie, 2 log-ins per week for 6 weeks; read 1 article per session). Control activities are designed to match the intervention condition in terms of time commitment and interface interaction, and to ensure consistent engagement across groups while allowing for the isolation of the impact of CarePair’s delivery and personalization features. During onboarding, participants are provided with a deidentified username and password to access the Digify platform, along with step-by-step instructions on the use of the platform.

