#### Primary Outcomes

##### Feasibility

Feasibility will be evaluated across recruitment, retention, and app usability. *Recruitment feasibility* [72] will be assessed by tracking the number and proportion of caregivers who (1) are eligible and consent, (2) are eligible and decline participation, and (3) are screened and found eligible. These metrics will be recorded in REDCap using timestamped research logs and will be used to calculate consent rates (eg, the number of consented individuals divided by the number of interested individuals). *Retention* will be examined via completion and attrition rates for the full sample and by study arm. We will calculate the number of completed assessments per participant divided by the total number of assessments, with attrition rates calculated as the proportion of noncompleters among enrolled participants. A designated data manager will oversee the collection, monitoring, and reporting of feasibility data.

*App feasibility* will be assessed through backend usage analytics (eg, number of log-ins and in-app interactions such as saving or reviewing resources). To assess *usability*, participants will complete a 10-item modified version of the System Usability Scale (SUS) [73,74], which measures usefulness, ease of use, and satisfaction at the posttest phase. Sample items include “I thought the CarePair app was easy to use” and “I felt very confident using the CarePair app.” Each item is rated on a 5-point Likert scale (1 [strongly disagree] to 5 [strongly agree]). Total scores are converted to a range from 0 to 100, with higher values indicating greater usability. At follow-up, participants will complete the 20-item user version of the Mobile Application Rating Scale (uMARS) [75], which evaluates app quality across 5 domains: engagement, functionality, esthetics, information, and subjective quality. Items such as “Is the app content (visuals, language, and design) appropriate for the target audience?” are rated on a 5-point Likert scale (1 [inadequate] to 5 [excellent]), with higher scores indicating higher perceived quality. These metrics will inform feasibility across recruitment, engagement, retention, and app usability, as well as guide modifications for a future large-scale trial.

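### The adherence outcome in Table 1 is not tied to the schedule that participants are asked to follow: two log-ins a week with one article read at each

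*Protocol article*

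**What the plan says.** The Study Conditions section asks participants in both arms to log in "twice per week and read 1 article per log-in (12 articles total across the intervention) for the 6-week study period". The Control Group section repeats the schedule for the Digify arm: "ie, 2 log-ins per week for 6 weeks; read 1 article per session". In the CarePair arm, the Intervention Group section also asks participants to engage with each article, with examples: "eg, by rating, commenting, saving, or taking notes".

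Table 1 (Assessments and Outcomes) places adherence under the primary feasibility outcomes and defines it as "Intervention adherence: app usage (measured via number of log-ins); feature usage (measured via number of interactions with resources [eg, saves and notes". The Feasibility section describes app feasibility in similar terms, through "backend usage analytics (eg, number of log-ins and in-app interactions such as saving or reviewing resources", and the Statistical Analysis section again gives log-ins and in-app actions as its examples of usage data.

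Both platforms record more than this. CarePair logs "participants’ number of log-ins, time spent engaging with materials, specific content accessed, and feature interactions". Digify offers "user-engagement tracking on metrics, including log-ins, articles read, and time spent viewing articles".

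**The concern.** The protocol gives participants an explicit schedule and then measures adherence by counts that omit two of its defining features: whether an article was opened, and how sessions were spread over the weeks. A log-in total cannot show whether caregivers read the material, or whether they kept going for six weeks rather than stopping after the first.

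This matters because adherence is a listed primary outcome. Under Principal Findings, the Discussion names it among the metrics expected to show strong feasibility, and among the indicators that will show whether CarePair can be delivered effectively. The control arm is also designed to match the intervention arm in time commitment, interaction frequency and engagement, so that the effect of delivery and personalization can be isolated. A measure of schedule completion common to both arms would let the report show how far that matching was achieved. The counts named in Table 1 offer only log-ins for this purpose.

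**Working it through.** **Inputs.** Two log-ins per week, one article per log-in, 6 weeks (Study Conditions; Control Group). Adherence counts as given in Table 1. Data logged by each platform as given in the Intervention Group and Control Group sections.

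**Step 1: the plan's own figure.** 6 weeks × 2 log-ins × 1 article = 12 articles. This agrees with the stated 12.

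**Step 2: a score tied to the schedule.** Let s_w be the number of sessions in study week w with a log-in and at least one article opened. Credit at most two per week:

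adherence = [min(2, s_1) + … + min(2, s_6)] / 12

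**Step 3: four usage patterns, each with 12 log-ins in total.** The patterns are illustrative assumptions, because the article reports no usage data.

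| Pattern | Total log-ins | Credited sessions | Share of schedule | Weeks with at least 2 credited sessions |
|---|---|---|---|---|
| 2 per week, article each time | 12 | 6 × 2 = 12 | 12/12 = 100% | 6 of 6 |
| 4 per week in weeks 1 to 3, article each time, then none | 12 | 3 × 2 = 6 | 6/12 = 50% | 3 of 6 |
| All 12 in week 1, article each time, then none | 12 | 1 × 2 = 2 | 2/12 = 16.7% | 1 of 6 |
| 2 per week, no article opened | 12 | 6 × 0 = 0 | 0/12 = 0% | 0 of 6 |

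The log-in count is the same in every row, while the share of the schedule completed runs from 0% to 100%.

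**Step 4: feature usage.** The caregiver in the first row, if she reads every article but saves and notes nothing and uses no other feature, has a feature-usage count of 0 despite completing 12 of 12 sessions. This count does not make good what the log-in total misses.

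**Step 5: what the two arms have in common.**

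| Quantity | CarePair | Digify |
|---|---|---|
| Log-ins | recorded | recorded |
| Articles or content opened | recorded (specific content accessed) | recorded (articles read) |
| Time on material | recorded | recorded |
| Saves, notes and similar interactions | recorded | not among the listed metrics |

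Of the two counts in Table 1, log-ins exist in both arms. Feature usage has no listed counterpart in the control arm. Article access, which both platforms record and which the schedule requires, is not named in the adherence definition.

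**The case against.** The strongest reply is that this article is condensed. Table 1 and the Feasibility section give examples rather than closed lists, and the latter mentions reviewing resources, which could mean opening an article. Because one article is prescribed per log-in, log-ins are a natural proxy for the schedule. Staff also follow log-in frequency during the study and use it to guide check-in emails (Retention and Adherence). Denominators and weekly windows may be set out in the full protocol or the analysis plan. On this view, what remains is a preference about reporting.

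Part of this stands. The absence of a cut-off or scoring rule is not a fault here. Several stronger readings that a reader might infer also fail:

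- **A single summed score that misclassifies people.** Table 1 lists two separate counts and no rule for calling anyone adherent, so no one is classified.
- **No comparison with the control arm is possible.** Log-ins are recorded on both platforms, and content opened could be compared too. Only feature usage lacks a counterpart. The outcome is also labelled as intervention adherence, and no between-arm comparison of it is promised.
- **Saves and notes are extraneous.** The Intervention Group section gives them as examples of the engagement requested with each article. The optional part is exploring service referrals.
- **Adherence drives the go/no-go decision.** The Sample Size section names recruitment, retention or attrition, and platform usability as the parameters informing progression. Adherence is not among them. Its role rests on the Discussion, which attaches no threshold to it.
- **Log-in counts wrongly penalise someone who reads 12 articles in 3 log-ins.** The schedule-based score also gives that person at most 3/12 = 25%, because the twice-weekly pattern was not followed.

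The reply does not remove the central point. Where the article says how adherence is measured, it names log-ins and feature interactions, and nowhere links adherence to the article or the week. The proxy argument assumes that each log-in leads to an article, which is part of what an adherence measure should establish.

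**Conclusion.** The concern holds in a limited form. The adherence measure in Table 1 does not capture the behaviour that the protocol assigns. The same 12 log-ins are compatible with 0% to 100% of the prescribed sessions, and feature usage can be zero for a caregiver who completes them all. How often such patterns occur is unknown, so the working shows what the count cannot distinguish and does not estimate the bias in this trial.

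The conclusion rests on Table 1 as published and takes the twice-weekly schedule as given. It is a weakness in a stated measure. It does not show that data will be lost, that the arms cannot be compared, or that the progression decision is compromised. It is worth correcting because adherence is a listed primary feasibility outcome and a measure closer to the assigned behaviour is available from data already described.

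**What to change.** Define adherence in the same way in both arms: sessions with a log-in and at least one article opened, credited up to 2 per study week, divided by 12. Beside it, report the number of distinct articles opened out of 12 and the number of weeks with any use. Keep total log-ins and feature usage (saves, notes, ratings, comments) as separately reported engagement data, with feature usage for the intervention arm only.

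The cost is a revised definition and some programming. No new data collection is described as necessary, and analysis is planned for August 2026, so the definition can be fixed and dated before then. One assumption should be checked first: weekly crediting needs date-stamped logs on both platforms, which the article does not state. If these are not available, distinct articles opened out of 12 can still be computed from the content data described. An opened article is also not proof of reading. Time on material, which both platforms record, can be reported descriptively to help with that. The downside is that the adherence figure may look less favourable than a log-in total.

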**Figure 2. F2:**
[figure not shown]
SPIRIT (Standard Protocol Items: Recommendations for Interventional Trials) checklist: CarePair trial assessments and timepoints. *Intervention group only.

#### Primary Outcomes

##### Feasibility

Feasibility will be evaluated across recruitment, retention, and app usability. *Recruitment feasibility* [72] will be assessed by tracking the number and proportion of caregivers who (1) are eligible and consent, (2) are eligible and decline participation, and (3) are screened and found eligible. These metrics will be recorded in REDCap using timestamped research logs and will be used to calculate consent rates (eg, the number of consented individuals divided by the number of interested individuals). *Retention* will be examined via completion and attrition rates for the full sample and by study arm. We will calculate the number of completed assessments per participant divided by the total number of assessments, with attrition rates calculated as the proportion of noncompleters among enrolled participants. A designated data manager will oversee the collection, monitoring, and reporting of feasibility data.

*App feasibility* will be assessed through backend usage analytics (eg, number of log-ins and in-app interactions such as saving or reviewing resources). To assess *usability*, participants will complete a 10-item modified version of the System Usability Scale (SUS) [73,74], which measures usefulness, ease of use, and satisfaction at the posttest phase. Sample items include “I thought the CarePair app was easy to use” and “I felt very confident using the CarePair app.” Each item is rated on a 5-point Likert scale (1 [strongly disagree] to 5 [strongly agree]). Total scores are converted to a range from 0 to 100, with higher values indicating greater usability. At follow-up, participants will complete the 20-item user version of the Mobile Application Rating Scale (uMARS) [75], which evaluates app quality across 5 domains: engagement, functionality, esthetics, information, and subjective quality. Items such as “Is the app content (visuals, language, and design) appropriate for the target audience?” are rated on a 5-point Likert scale (1 [inadequate] to 5 [excellent]), with higher scores indicating higher perceived quality. These metrics will inform feasibility across recruitment, engagement, retention, and app usability, as well as guide modifications for a future large-scale trial.

##### Acceptability

Acceptability will be assessed at the 6-week follow-up using an 8-item survey measuring user satisfaction, usefulness, and ease of use. Participants will rate their agreement with statements such as “I was satisfied with the features in the CarePair application” and “Using the CarePair application was worth my time” on a 5-point Likert scale (1 [strongly disagree] to 5 [strongly agree]). In addition, CarePair intervention participants will complete 4 open-ended questions providing qualitative feedback on their experiences, including which features were engaging, helpful, or in need of improvement. Sample prompts include the following: “Which CarePair features did you find most valuable? Why?”

### Secondary Outcomes

#### Caregivers’ Needs

Caregivers’ needs will be assessed and compared at baseline and follow-up using a 12-item needs assessment developed for this study. The CarePair Needs Assessment measures caregivers’ needs across a variety of caregiving domains, such as social support, legal guidance, and education. Questions, including “In your role as a caregiver, how much support do you need with connecting with others who are in similar care situations?” are rated from 1 (no need) to 4 (high need). Scores range from 12 to 48, with higher scores indicating greater need.

#### Self-Efficacy

Caregiving self-efficacy will be measured at baseline and follow-up using the 15-item Revised Scale for Caregiving Self-Efficacy [81]. Items assess caregivers’ confidence in managing their own lives in addition to care-related responsibilities (eg, “How confident are you that you can ask a friend/family member to stay with [care recipient] for a week when you need time for yourself?”). Responses are rated from 0 (cannot do at all) to 100 (certainly can do). Total scores range from 0 to 100, with higher scores indicating greater perceived self-efficacy (Cronbach α=0.80).

#### Anxiety

Anxiety symptoms will be assessed using the Generalized Anxiety Disorder-7 (GAD-7) [78]. Participants report how frequently they experienced symptoms (eg, worrying and difficulty relaxing) in the past 2 weeks (eg, “Over the last 2 weeks, how often have you been bothered by... feeling nervous, anxious, or on edge?”). Items are rated on a 4-point scale (0 [not at all] to 3 [nearly every day]). Total scores range from 0 to 21, with higher scores indicating greater anxiety (Cronbach α=0.92).

